15 APPENDICES LIST …………………………………………………………………………………………………………..……….33

LIST OF ABBREVIATIONS

| AE | Adverse Event/Adverse Experience |
| --- | --- |
| CONSORT | Consolidated Standards of Reporting Trials |
| CRF | Case Report Form |
| CPLE | *Carica papaya* leaf extract |
| GCP | Good Clinical Practice |
| ICF | Informed Consent Form |
| ICH | International Conference on Harmonization |
| IRB | Institutional Review Board |
| LFT | Liver Function Tests |
| AST | Aspartate Aminotransferase |
| ALT | Alanine Aminotransferase |
| MOP | Manual of Procedures |
| N | Number (typically refers to subjects) |
| PI | Principal Investigator |
| SAE | Serious Adverse Event/Serious Adverse Experience |
| SOP | Standard Operating Procedure |
| UP | Unanticipated Problem |
| WHO | World Health Organization |

PROTOCOL SUMMARY

| **Title:** | A prospective study to evaluate the safety and efficacy of *Carica papaya* leaf extract (oral CPLE (Caripill)) in the treatment of severe thrombocytopenia (≤30,000/µl) in dengue |
| --- | --- |
| **Précis:** | This will be a placebo-controlled, single center, randomized prospective study of CPLE (Caripill) (*Carica papaya* leaf extract) tabs in dengue patients with severe thrombocytopenia (platelets ≤ 30,000/ul). The study will enroll 100 eligible dengue cases into the two arms of the study – one arm receiving CPLE (Caripill) 1100mg *t.i.d* for 5 days and the other group receiving placebo. |
| **Objectives:** | Primary: To determine the impact of CPLE (Caripill) administration (1100mg *t.i.d* for 5 days on the following:   - Platelet count and hematocrit values in dengue patients with severe thrombocytopenia. - Reducing the number of blood product transfusions *esp.* platelet transfusion and - All-cause mortality rates. |
|  | Secondary: To evaluate the effect of CPLE (Caripill) administration (1100mg *t.i.d* for 5 days) on the following-   - Magnitude and kinetics of serum viremia (or NS1 antigenemia). - Magnitude and kinetics of cytokines IFNγ, IL6, TNFα and IL4. - The total length of hospital (ICU & ward) stay, |
| **Population:** | Study cohort of 100 adults, either gender (more than 18 yrs old, non-pregnant) and admitted to AIMS Hospital and diagnosed of dengue with moderate to severe thrombocytopenia. |
| **Number of Sites:** | Dept. of General Medicine and Dept. of Emergency Medicine, Amrita Institute of Medical Sciences and Research Center, [name]. |

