1. OBJECTIVES
   1. Study Objectives

Thrombocytopenia is a well-known risk factor of fatality in severe dengue cases. A steady decline in platelet counts is characteristically associated with dengue illness severity. Thrombocytopenia coupled to severe vascular leakage and shock, usually around the time of defervescence can prove to be fatal. We hypothesize that administration of CPLE (Caripill) tab early in the course of dengue illness increase the platelet counts and reduce the likelihood of severe complications.

The clinical benefit of CPLE (Caripill) administration on the platelet counts in mild and moderate dengue have been shown before, this study will present an opportunity to specifically evaluate the effectiveness of CPLE (Caripill) administration in severe thrombocytopenic (≤ 30,000/µL) dengue cases. We will also investigate the effect of CPLE on the viremia (or NS1 antigenemia) as well as the infection induced immune response.

Primary Objectives:

1. To evaluate if CPLE (Caripill) administration (1100 mg three times a day for 5 days) in dengue patients with thrombocytopenia ≤30,000/µL is superior to placebo with respect to improvement in platelet counts and hematocrit values.
2. To evaluate if CPLE (Caripill) administration (1100mg three times a day for 5 days) in dengue patients with thrombocytopenia ≤30,000/µL is superior to placebo with respect in reducing the number of platelet transfusions needed in management.
3. To determine and compare the incidence of bleeding episodes during hospitalization between the treatment and placebo groups. Bleeding will be defined as mucosal bleeds such as subcutaneous bleeding, minor mucosal hemorrhages, sub-conjunctival hemorrhage, epistaxis, petechiae, or ecchymosis, positive tourniquet test.
4. To evaluate the final outcome of dengue illness (survival/mortality rates) between the treatment and placebo groups.

Secondary Objectives:

1. To correlate the changes in platelet counts to the clinical phase of dengue illness (febrile/critical (plasma leak)/ convalescent) between the treatment and placebo groups.
2. To compare and evaluate the viremia (or NS1 antigenemia) with peripheral platelet counts between the treatment and placebo groups.
3. To evaluate length of hospital (ICU & ward) stay in patients receiving CPLE (Caripill) for severe dengue.
4. To compare and evaluate the levels cytokines TNFα, IFNγ, IL4 and IL6, on day 0, and 3 of study period between the treatment and placebo groups.

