   1. Study Outcome Measures
      1. Primary

The primary efficacy endpoints will be assessed by comparing the increase in the platelet counts and hematocrit levels during the hospital stay between the treatment and placebo groups. The peak platelet count and hematocrit will also be noted and compared between the treatment and the placebo group. Additionally, the frequency and type of blood product, more specifically platelet transfusions required to manage thrombocytopenia during the course of illness will be compared between the two study arms.

Safety and tolerability will also be evaluated by comparing the proportion of patients with any AE (adverse event), and with any SAEs, between the treatment arms. The incidence of bleeding episodes as assessed by clinical evaluation twice daily between the treatment and placebo groups will also be evaluated. Evidences of subcutaneous bleeding minor mucosal hemorrhages, sub-conjunctival hemorrhage, epistaxis, petechiae, or ecchymosis), positive tourniquet test, hypotension and internal organ bleeding, hematemesis, intracranial bleed and melena will be assessed.

- - 1. Secondary

Secondary outcomes that we plan to evaluate include parameters indicative of disease progression or worsening of illness. These will be compared between the two study arms.

1. To correlate the change in platelet counts and subsequent response with or without CPLE (Caripill) to the phase of dengue (febrile/critical (plasma leak)/ convalescent) We will study the correlation of the duration of moderate to severe thrombocytopenia with the phase of the dengue- febrile, critical-plasma leak, convalescence. Additionally we will compare both arms of the study to examine if the intervention in any of the three phases affected the duration/severity of thrombocytopenia.
2. The type of bleeding manifestation between the two arms of the study will be characterized. We will examine the evidence of (mucosal, GI, GU, vaginal, IC bleed etc.) bleeding with severity of thrombocytopenia and response to intervention by comparing both arms.
3. Date of admission and date of discharge or death will be noted in the CRFs and will be used to determine the length of hospital stay (ICU & Ward), in severe thrombocytopenic dengue patients receiving CPLE (Caripill) treatment compared to the placebo group.

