**10.4: Interim Analyses:**

An interim efficacy analysis based on the primary outcome will occur when 30% of the patients have been followed. The Haybittle-Peto rule will be applied to evaluate the efficacy of between the two treatment groups i.e. interim analysis shows a probability of equal to, or less than 0.001 between the two groups.

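### The Summary, 3.1 and 3.2.1 give three different, unranked primary sets, so the primary outcome that the 10.4 interim rule uses is never identified

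*Protocol*

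**What the plan says.** **Protocol Summary.** The primary objectives are platelet count and hematocrit, transfusions ("Reducing the number of blood product transfusions", with platelets emphasised) and "All-cause mortality rates". Bleeding is not listed.

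**Study Objectives (3.1).** There are four primary objectives:
- whether CPLE "is superior to placebo with respect to improvement in platelet counts and hematocrit values";
- superiority in reducing the number of platelet transfusions;
- comparison of the incidence of bleeding;
- mortality: "To evaluate the final outcome of dengue illness (survival/mortality rates) between the treatment and placebo groups".

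Bleeding is described thus: "Bleeding will be defined as mucosal bleeds such as subcutaneous bleeding, minor mucosal hemorrhages, sub-conjunctival hemorrhage, epistaxis, petechiae, or ecchymosis, positive tourniquet test".

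**Study Outcome Measures, Primary (3.2.1).** "The primary efficacy endpoints will be assessed by comparing the increase in the platelet counts and hematocrit levels during the hospital stay". Peak platelet count and peak hematocrit are compared as well, and so are the frequency and type of transfusion. A second paragraph, on safety and tolerability, covers adverse events, serious adverse events and bleeding. Its list of signs repeats the minor ones and ends: "positive tourniquet test, hypotension and internal organ bleeding, hematemesis, intracranial bleed and melena will be assessed". Mortality does not appear.

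**Section 10.1.** The stated 80% power is for a 20% increase in platelet count and hematocrit together.

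**Section 10.4.** "An interim efficacy analysis based on the primary outcome will occur when 30% of the patients have been followed". The threshold is a probability of 0.001 or less under the Haybittle-Peto rule.

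**The concern.** An efficacy stopping rule needs one named outcome, and so does the headline claim of a superiority trial. Here the answer depends on the section that is read. Whoever runs the interim must choose the endpoint. At the end, a favourable result on any of several endpoints could be presented as the primary result with support from some part of the protocol. Without a ranking or a division of the error rate, the chance of a false claim exceeds the level used for each test.

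Two related points follow. Mortality is given primary status in two sections although a trial of this size can say almost nothing about it. The incidence of bleeding could also differ according to whether 3.1 or 3.2.1 is followed.

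**Working it through.** **1. The three lists side by side**

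| Item | Summary | 3.1 | 3.2.1 (Primary) |
|---|---|---|---|
| Platelet count | primary | primary | primary (increase) |
| Hematocrit | primary | primary | primary (increase) |
| Peak platelets, peak hematocrit | – | – | compared |
| Transfusions | blood products | platelets | blood products by type, chiefly platelets |
| Bleeding | – | primary | under safety |
| Mortality | primary | primary | – |
| AEs, SAEs | – | – | under safety |

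Platelets, hematocrit and transfusions are common to all three. Mortality, bleeding and the peaks are not. No section ranks the items.

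**2. Does the stated power identify the primary outcome?**
Inputs: 50 per arm (study schematic) and a 20% increase with 80% power (10.1). Neither the SD nor the significance level is given, so the 80% cannot be reproduced. At an assumed two-sided 5%, the detectable standardised difference is (1.960 + 0.842) × √(2/50) = 0.560, which requires a coefficient of variation of 0.20/0.560 = 0.357. The statement covers both platelets and hematocrit. It narrows the candidates to two but does not select one.

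**3. Error rate at the final analysis**
Assumption: each comparison is tested at two-sided 5%. The correlated columns assume equal pairwise correlation.

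| Comparisons | Independent, 1 − 0.95^k | Correlation 0.5 | Correlation 0.7 |
|---|---|---|---|
| 3: superiority wording only (platelets, hematocrit, platelet transfusions) | 14.3% | 12.5% | 10.9% |
| 5: all of 3.1 | 22.6% | 18.3% | 14.8% |
| 7: 3.1 pooled with the two peaks of 3.2.1 | 30.2% | 23.0% | 17.8% |

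The endpoints are probably positively correlated, so the independent column is the upper end.

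**4. Error rate at the interim**
At a threshold of 0.001, five candidates give at most about 1 − 0.999^5 = 0.5%, and seven give 1 − 0.999^7 = 0.7%.

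**5. Mortality**
Inputs: 50 per arm, and the 2.5% case fatality for dengue in general cited in Background Information. Expected deaths at that rate are 0.025 × 50 = 1.25 per arm. With 50 per arm, two-sided Fisher's test gives p = 0.056 for 5 against 0 deaths and p = 0.027 for 6 against 0, so 6 against 0 is the smallest such split below 0.05. Exact power follows; the control rates above 2.5% are assumptions.

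| Control death rate | Power if halved | Power if all deaths are prevented |
|---|---|---|
| 2.5% | 0.1% | 0.2% |
| 5% | 1.2% | 3.8% |
| 10% | 6.3% | 38% |
| 15% | 12.4% | 78% |

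**6. Bleeding**
Section 3.1 names mucocutaneous signs and a positive tourniquet test. Section 3.2.1 names those and adds internal organ bleeding, hematemesis, intracranial bleed, melena and hypotension. A tourniquet test is a bedside test and hypotension is a hemodynamic sign; neither is itself a clinical bleed.

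**The case against.** The strongest reply is that the lists overlap more than they differ. All three contain platelets, hematocrit and transfusions. Section 3.2.1 opens with the increase in platelets and hematocrit as the primary efficacy endpoints, and 10.1 powers those two. Only the first two objectives in 3.1 use superiority language. Section 10.1 calls the study exploratory, and 10.3 promises a detailed analysis plan before unblinding, where a multiplicity method may properly sit. Deaths are captured in any case, as an outcome in the data section and as grade 5 events.

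Much of this stands. It reduces the likely candidates to platelets and hematocrit. It does not choose between them, or between increase and peak, and it does not explain why mortality and bleeding change status between sections. An analysis plan can add a method, but it should not have to decide which protocol list is the primary one. The exploratory label sits awkwardly with superiority objectives and an efficacy interim.

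Some stronger readings are tempting but are not supported:
- **Seven declared primary tests.** No section lists seven; that count comes only from pooling 3.1 and 3.2.1.
- **A lost 5% level.** The protocol states no final level, so 5% is an assumption here.
- **An interim with 15-30% false stopping.** Those figures concern final tests. At 0.001 the figure is at most about 0.7%.
- **Major bleeds ignored.** 3.1 offers its list as examples, 3.2.1 names major bleeds under the Primary heading, and a secondary outcome covers bleeding by type. The fault is a mismatch, and it is not the reason the interim rule lacks a named outcome.
- **Minor signs at entry overwhelming serious bleeds.** The documents give no figure for this.

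**Conclusion.** The point holds as an internal contradiction. Three sections give three different, unranked primary sets, and the 10.4 efficacy rule refers to a single primary outcome that none of them identifies. The damage is chiefly to the final claim. On an assumed two-sided 5% level, the chance of at least one false positive is 22.6% for the five comparisons in 3.1 if independent (about 15-18% at correlations of 0.7-0.5), and up to 30% if 3.1 and 3.2.1 are pooled. At the interim the problem is an undefined rule, not a large error rate.

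Mortality is not a workable primary endpoint with 50 per arm. This is firm at the cited 2.5% and for a halving of any assumed rate up to 15%. The 2.5% is for dengue in general, and no rate is given for platelets of 30,000/µL or below. Only near-complete prevention from a much higher assumed rate would be detectable. The bleeding mismatch is real but separate and smaller.

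**What to change.** Name one primary outcome in the same words in the Summary, 3.1, 3.2.1, 10.1 and 10.4. One example is the increase in platelet count from baseline to study day 5, adjusted for baseline. Daily platelet counts (section 8) and daily follow-up to day 5 even after discharge (Study Design) make this obtainable. State how counts taken after a platelet transfusion are handled, because a transfusion raises the count and is itself an outcome.

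Place hematocrit, platelet transfusions and bleeding as secondaries tested in a fixed order. Report mortality descriptively. Apply the 0.001 interim rule to the one primary outcome only, and state the final significance level.

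Separately, use one definition of clinical bleeding throughout. It should include the major bleeds named in 3.2.1, with tourniquet test and hypotension reported on their own.

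The cost is amendment wording, best done before the interim look, and fewer endpoints that can be called primary. The case report form is not among the documents at hand, so check that it records bleeding in enough detail for the single definition. Keeping all five items of 3.1 as primary with a Bonferroni split would cost more: each test at 0.05/5 = 0.010 takes an endpoint with exactly 80% power at 5% down to about 59%, and about 75 per arm would be needed to restore it.

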5. STUDY DESIGN

This study is a randomized, placebo-controlled; double-blind trial investigating CPLE (Caripill) therapy in adult dengue patients with a thrombocytopenia of < 30,000/µL. Adults (≥ 18yrs of age, non-pregnant) and laboratory (+ NS1 ELISA/ + vRNA RTPCR)/+IgM or +IgG) confirmed diagnosis of dengue and with a peripheral platelet count of ≤ 30,000/µL will be enrolled into the study after signing an informed consent form.

The study patients will be followed for clinical and laboratory endpoints in hospital until study day 5 (or daily as out-patients from discharge to day 5) and reviewed at an outpatient visit at week 2.

The patients will be assigned to one of the two treatment arms:

1. Active drug: CPLE (Caripill) CPLE 1100mg *t.i.d* for 5 days.

2) Placebo: visually matched placebo *t.i.d* for 5 days.

Oral tablet of CPLE (Caripill) and placebo will be provided by Micro Labs Ltd with appropriate masking for a double blind study. On receipt the medications will be stored in accordance with the manufacturer’s recommendation in a secure area.

Enrolled patients will be randomly assigned in a 1:1 ratio to receive CPLE (Caripill) or placebo once daily for 5 days. Online randomization software will be used for patient assignment. Only the clinical trials pharmacist will have access to the randomization list.

Micro Labs Ltd will provide CPLE (Caripill) and visually matched placebo without charge. All other study staff will be blinded to treatment allocation until after completion of the study. Each enrolled patient was assigned the next available study code that corresponded to a prepackaged pack of study drug. Clinical data were captured on structured case report forms that were entered into a secure database.

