**5.4 Treatment Assignment Procedures**

- 1. 1. Randomization Procedures (if applicable)

We will randomly assign enrolled patients in a 1:1 ratio to receive CPLE (Caripill) (1100mg) or placebo once daily for 5 days. Block randomization of will be stratified by age and gender into block sizes of 4 or 6.

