**10.3: Sub-group Analyses:**

Pre-defined secondary endpoints will be compared between the two treatment arms based on linear regression for continuous endpoints, logistic regression for binary endpoints, and Cox regression for time-to-event endpoints. For laboratory markers, comparisons will be adjusted for the pre-dose value of the respective marker and the day of illness at enrolment; plasma cytokines and NS1-endpoints will additionally be adjusted for dengue illness phase.

A detailed statistical analysis plan will be finalized prior to unblinding the study data base.

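### The primary platelet increase is measured over the hospital stay, which the drug may shorten, so a real benefit can be diluted; the planned follow-up to study day 5 allows a fixed-day endpoint instead

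*Protocol*

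**What the plan says.** Under Study Outcome Measures, Primary, the protocol says: "The primary efficacy endpoints will be assessed by comparing the increase in the platelet counts and hematocrit levels during the hospital stay", the comparison being between the two arms. It adds: "The peak platelet count and hematocrit will also be noted and compared between the treatment and the placebo group". No time point is named for either measure, and the peak has no stated window.

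The same section makes two post-randomisation quantities outcomes in their own right. Admission and discharge dates "will be used to determine the length of hospital stay (ICU & Ward", a secondary comparison between arms. Among the primary comparisons, "platelet transfusions required to manage thrombocytopenia during the course of illness will be compared between the two study arms".

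The Study Design section sets a different window. Patients are followed for clinical and laboratory endpoints "in hospital until study day 5 (or daily as out-patients from discharge to day 5", with a further visit at week 2. Clinical Laboratory Evaluations plans platelet counts at least daily.

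On the model, section 10.2 gives an intention-to-treat comparison of the two arms and names no method for the platelet endpoint. Section 10.3 says that for laboratory markers "comparisons will be adjusted for the pre-dose value of the respective marker and the day of illness at enrolment", but this follows a sentence on secondary endpoints under a sub-group heading. Section 5.4 says that block randomisation "will be stratified by age and gender into block sizes of 4 or 6"; neither factor appears in a stated model. Section 10.3 promises a detailed SAP before unblinding, which is not at hand.

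**The concern.** The background section says that platelets fall and then return to normal as the fever subsides. During recovery, an increase therefore depends on how long the patient is watched. The protocol ties that time to the hospital stay. The stay is something the drug may change: the protocol compares it between arms and cites an earlier study of the extract that reported shorter stays.

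A patient who recovers fast and goes home early has fewer days in which to show an increase, while a slow recoverer is watched until the count comes up. If the drug works, the endpoint gives away part of its own effect. Platelet transfusion can act in the same direction: it raises the measured count, and a working drug should make it rarer on active treatment. What is at stake is a missed benefit in a trial of 50 per arm.

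**Working it through.** **1. The windows side by side.** The endpoint runs to discharge; the follow-up runs to study day 5 whatever the discharge date. The two coincide only if nobody leaves before day 5 and counts after day 5 are not used. Section 8.1 has an incomplete sentence pointing to discharge on or after day 5. Study Design and Clinical Laboratory Evaluations both allow for earlier discharge.

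**2. The plan's own figure.** Section 10.1 claims 80% power for a 20% increase. It gives no SD, no final alpha and no base for the 20%, so the figure can be neither reproduced nor refuted. Solving backwards at two-sided 0.05 (assumed) with 50 per arm:

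CV = 0.20 / [(1.96 + 0.842) × √(2/50)] = 0.20 / (2.802 × 0.2) = 0.357.

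**3. Effect of the window.** The protocol gives no recovery data, so the simulation inputs are assumptions and show direction only: 50 per arm; baseline uniform on 10 to 30 thousand/µL; recovery starting after 0 to 2 days; placebo daily rise log-normal with median 14 thousand/µL and log-SD 0.5; measurement SD 4 thousand/µL; drug effect a 30% faster rise; t-test, 1,000 runs. Hand check of the day-5 difference: 14 × exp(0.5²/2) = 15.9 per day; 0.3 × 15.9 × 4 mean days of recovery ≈ 19 thousand/µL.

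| Discharge rule (assumed) | Increase to discharge: difference, power | Increase to day 5: difference, power |
|---|---|---|
| At 50,000/µL, from day 2 | 2.9 thousand, 21% | 19.0 thousand, 66% |
| At 50,000/µL, not before day 5 | 18.0 thousand, 63% | 19.0 thousand, 65% |

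The peak up to discharge, under the first rule, gave 2.9 thousand and 29% power.

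With no drug effect, and so the same discharge rule and transfusion rate in both arms, the mean difference was close to zero. The discharge-based increase and peak rejected in 4.2% to 5.3% of runs against a nominal 5% (Monte Carlo standard error about 0.7 points).

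**4. Effect of transfusion.** Assume 30% of placebo and 15% of active patients are transfused, each gaining a lasting 20 thousand/µL, with counts used as observed. The shift is (0.30 − 0.15) × 20 = 3 thousand/µL against the drug. The simulated day-5 difference fell from about 19 to about 16 thousand/µL and power from about 66% to 47%. A fixed day does not remove this effect.

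**5. Effect of adjustment.** Let k be baseline SD over follow-up SD and r their correlation. Relative to the follow-up variance, a change score has variance 1 + k² − 2rk and ANCOVA has 1 − r². Power at CV 0.357 and 50 per arm:

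| k, r | Change score | ANCOVA | Gain in points |
|---|---|---|---|
| 0.2, 0 | 78.4% | 80.0% | 1.6 |
| 0.2, 0.3 | 83.2% | 83.6% | 0.4 |
| 0.2, 0.5 | 86.4% | 89.9% | 3.5 |
| 0.3, 0.3 | 83.6% | 83.6% | 0.0 |
| 0.5, 0 | 70.7% | 80.0% | 9.3 |

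Entry at or below 30,000/µL limits baseline spread, so small k is the likelier case. Any gain from day of illness, age and gender is not included.

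**The case against.** The strongest reply is that the trial may in practice keep nearly everyone to day 5. The loss is then about 1 thousand/µL and 2 points of power. That stands. But the protocol itself provides for earlier discharge, so the endpoint should not depend on it not happening.

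A second reply is that covariates, the primary model and the handling of transfused counts are commonly left to a SAP. That also stands: their absence is not an error in itself. The window is different, because the protocol states it and a later section of the same document offers a better one.

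Several stronger readings are tempting but are not supported:

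- A reader might infer that an ineffective drug could look different through discharge practice. One could argue that a day less in hospital at a 20% to 40% daily rise lowers the peak by 1 − 1/1.2 = 17% to 1 − 1/1.4 = 29%. This imposes a shorter stay on one arm despite identical recovery. With double-blind 1:1 allocation the documents give no route to that.
- A reader might infer that a true benefit could be reversed. The scenarios run show attenuation towards zero, not reversal.
- A reader might infer that transfused platelets are scored as recovery. The protocol does not say so; it is silent.
- A reader might call the endpoint unadjusted and therefore biased. An increase already subtracts baseline, section 10.3 can be read to cover platelets, and in a randomised trial missing adjustment costs precision, not validity.

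**Conclusion.** The point holds in a limited form. The stated window lets a post-randomisation outcome decide how long each patient's increase is observed, and it does not match the protocol's own follow-up to day 5. The consequence is dilution of a real benefit, not a false claim of efficacy. Its size ranges from negligible when nobody leaves before day 5 to most of the effect (about 19 down to 3 thousand/µL) under an assumed early, count-driven discharge rule.

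Unequal transfusion would add dilution of about 3 thousand/µL at the assumed rates, provided counts are used as observed. The unclear scope of the baseline adjustment costs about 0 to 9 power points against a change score in the cases run. All these sizes rest on assumed recovery, discharge, transfusion and correlation values, because the protocol gives none.

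**What to change.** - Define the primary platelet endpoint as the log count at study day 5, using the out-patient count for anyone discharged earlier, and use the same window for hematocrit. Say how study day 5 is counted from first dose: the schematic appears to start dosing on day 0 and the Study Schedule section on day 1, and these must be reconciled.
- Analyse by ANCOVA, or by a mixed model over days 1 to 5 with the day-5 contrast as primary, adjusted for baseline count, day of illness at enrolment, age and gender. State that the section 10.3 adjustment applies to the primary endpoint.
- Make the peak count descriptive.
- Add a sensitivity analysis for counts taken after a platelet transfusion. Do not rank transfusion as the worst outcome inside the ANCOVA: a rank does not fit a model for log counts, and it would count the separate transfusion objective twice.
- Reconcile the incomplete discharge sentence in section 8.1 with the Study Design section.

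The cost is protocol and SAP wording, since the counts are already planned. The downside is a few missed day-5 out-patient counts. The change should be made before the interim efficacy analysis in section 10.4, which uses the primary outcome once 30% of patients have been followed.
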